**Figure 1 figure1:**
[figure not shown]
Flowchart of patient enrolment and evaluation. CT: computed tomography; MRI: magnetic resonance imaging; MRCP: magnetic resonance cholangiopancreatography; ERCP: endoscopic retrograde cholangiopancreatography; EUS: endoscopic ultrasound; EUS-FNA: endoscopic ultrasound-guided fine needle aspiration; US: ultrasound.

### Diagnostic Procedures

Diagnostic data will be collected from patients referred to Mie University Graduate School of Medicine and will include the outcomes of routine EUS, dynamic CT, and MRI or magnetic resonance cholangiopancreatography assessments. Confirmatory diagnostic tests will include endoscopic retrograde cholangiopancreatography and endoscopic ultrasound-guided fine needle aspiration. Biopsy samples collected during EUS-FNAB will be fixed in alcohol and stained using the Papanicolaou multichromatic procedure. The remaining material will be fixed in 10% formalin and embedded in paraffin for cell block analysis to obtain histological diagnosis using hematoxylin and eosin staining. Tumor staging will be performed according to the UICC-American Joint Committee on Cancer tumor, node, and metastasis categories [16].

### Follow-Up Assessments

Patients with a diagnosis of pancreatic cancer will undergo appropriate treatment (eg, surgery and/or chemotherapy) according to the standard of care guidelines [11]. Patients with negative diagnostic results will be followed by contract CT, abdominal ultrasound, and/or MRI. Blood testing for carcinoembryonic antigen (CEA), carbohydrate antigen 19-9 (CA19-9), amylase, and lipase will be performed at intervals of 6 months.

### Study Endpoints

The primary endpoint is the diagnosis rate (number of patients diagnosed/total number of study participants) for pancreatic cancer, calculated with a 95% CI. The secondary endpoints include the diagnosis rates of pancreatic cancer by stage, pancreatic neoplasms other than pancreatic ductal adenocarcinoma, Stage 0/I pancreatic cancer at each visit, and surgical resection. For patients with a definite diagnosis of pancreatic cancer, a frequency table will be created based on the resectability classification [16].

### Sample Size

We based our sample size on data from a previous study, in which 28 patients were diagnosed with pancreatic cancer among 224 subjects who had 2 or more pancreatic cancer risks [14]. The risks prespecified in this study are considered equivalent to those reported previously, meaning that the rate of the patients diagnosed with pancreatic cancer is expected to be approximately 10%. To obtain estimation accuracy (95% CI) of ±5%, the required number of subjects is calculated as 138. The planned number of participants in this study is 150. We expect that approximately 100-150 patients with ≥2 points on the pancreatic cancer risk scoring metric will visit the participating clinics per year and that 80% of these eligible patients will give consent to participate in the study [14]. Therefore, in the 2-year referral period, 160-240 participants are expected to enroll in this study. However, when the number of patients reaches 150, registration will continue because this a prospective observational study without any intervention.

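### The sample size plans on a 10% diagnosis rate without a reason, although the cited data give 12.5%; at 12.5%, ±5 points needs 169 participants rather than 138

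*Protocol article*

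**What the plan says.** The primary endpoint, under Study Endpoints, is a single proportion: "The primary endpoint is the diagnosis rate (number of patients diagnosed/total number of study participants) for pancreatic cancer, calculated with a 95% CI".

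The Sample Size section argues in four steps:

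- Source: "28 patients were diagnosed with pancreatic cancer among 224 subjects who had 2 or more pancreatic cancer risks".
- Transfer to this study: "The risks prespecified in this study are considered equivalent to those reported previously".
- Planning rate, presented as what that equivalence implies: "the rate of the patients diagnosed with pancreatic cancer is expected to be approximately 10" percent.
- Requirement: "To obtain estimation accuracy (95% CI) of ±5%, the required number of subjects is calculated as 138".

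It then sets the size, "The planned number of participants in this study is 150", and describes accrual: "in the 2-year referral period, 160-240 participants are expected to enroll in this study". There is no cap, since "when the number of patients reaches 150, registration will continue". Study Design and Population and Results both present 150 as a minimum.

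**The concern.** The step from the source data to the planning rate does not follow. Equivalent risks would carry the source rate over unchanged, and 28/224 is 12.5%. The article mentions no discount, difference in case mix or other reason for going lower.

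The direction matters. Below 50% the binomial variance p(1−p) rises with p, so a lower planning rate gives a smaller required number and a narrower stated interval. The article gives no hypothesis test or power for the primary endpoint, so the ±5 points is the only quantitative basis for the sample size. The Discussion also says that diagnosis rates can be compared with historic published data. A reader making that comparison should know what precision to expect at the rate the source supports.

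**Working it through.** **Inputs, all from the Sample Size section.** Source 28/224; planning rate 10%; half-width d = 0.05 with 95% confidence (z = 1.96); required number 138; planned number 150; expected enrolment 160-240. That range is consistent with the section's own figures: 100-150 eligible per year × 2 years × 80% consent = 160-240.

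**Source rate.** 28/224 = 0.125, or 12.5%.

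**Reproducing the plan's figure.** For one proportion with a normal-approximation (Wald) interval, n = z²·p(1−p)/d².

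- p = 0.10: 3.8416 × 0.0900 / 0.0025 = 138.3. This matches the stated 138 (139 if rounded up, which is immaterial).
- Other intervals at 10%, for a total width of at most 10 points, need 141 (Wilson) or 158 (exact). The plain Wald formula is therefore the one that fits, and it is used throughout below.

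**Same formula at the source rate.**

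- p = 0.125: 3.8416 × 0.109375 / 0.0025 = 168.1, so 169.
- 169/138 = 1.22 and 169/150 = 1.13, so 169 is 22% above the calculated number and 13% above the planned number.

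**Half-width, 1.96·√(p(1−p)/N), in percentage points.**

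| N | at 10% | at 12.5% |
|---|---|---|
| 138 (calculated) | 5.01 | 5.52 |
| 150 (planned minimum) | 4.80 | 5.29 |
| 160 (low end expected) | 4.65 | 5.12 |
| 169 | 4.52 | 4.99 |
| 200 (midpoint expected) | 4.16 | 4.58 |
| 240 (high end expected) | 3.80 | 4.18 |

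**Rate at which ±5 points is lost.** Solving p(1−p) = N × 0.0025/3.8416 for p gives about 11.0% at N = 150 and about 11.8% at N = 160. Both are below 12.5%.

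**Uncertainty of the source rate.** The 95% interval for 28/224 is 8.8% to 17.5% (Wilson). At N = 150 its ends give 1.96·√(0.088 × 0.912/150) = ±4.5 points and 1.96·√(0.175 × 0.825/150) = ±6.1 points.

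**The case against.** The strongest reply is that the calculation itself is sound. For the rate the article states, 138 is the right number, and 150 meets the target with a little to spare (±4.80). The rate is worded as an approximate expectation, and 10% lies inside the source study's own interval. A lower rate is not implausible either: under Study Design and Population, pancreatic duct dilation or a cyst alone scores 2 points, so a single finding can qualify a participant, whereas the source group is described as having two or more risks. Accrual is also open-ended, and 169 sits near the bottom of the expected 160-240. Finally, no decision threshold depends on the interval, which will be reported at whatever width results.

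Most of this stands, and it limits the size of the point. A reader might infer that 138 is an arithmetic error, that 150 participants cannot deliver ±5 points, or that enrolment must be raised. The documents support none of these: the figure reproduces at the stated rate, the shortfall arises only if the true rate is above about 11%, and registration already continues past 150.

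What the reply does not repair is the inference in the text. The article offers neither sampling uncertainty nor broader entry as its reason for 10%. It says the risks are equivalent and presents 10% as the consequence. Whether entry really is broader than in the source study cannot be checked here, because the source's scoring is not given. The source interval also extends further above 10% than below it, so it does not by itself favour the lower figure.

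**Conclusion.** The planning rate is not the one the cited data give, and no reason is stated for the difference. That part is certain from the Sample Size section alone.

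The effect on precision is conditional on the true rate being 12.5% and on a Wald interval, the method that reproduces 138. Under those assumptions ±5 points is missed by about 0.5 points at 138, 0.3 at 150 and 0.1 at 160. It is reached at 169, within expected enrolment. At 10% the planned 150 meets the target. This is a small misstatement in the justification of the sample size and worth correcting. It is not a failure of the design.

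**What to change.** Revise the Sample Size section in one of two ways:

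- State the source rate as 12.5% (28/224), and give the planned precision as about ±5.3 points at 150 and ±5.1 to ±4.2 points over the expected 160-240. Note that ±5 points corresponds to 169 participants at that rate.
- Keep 10%, label it a discounted assumption, give the reason, and show the precision at both rates: ±4.8 points at 10% and ±5.3 points at 12.5% for 150 participants.

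Either is a change of wording. No additional enrolment is needed, because registration already continues beyond 150. The only downside is a slightly less favourable stated precision.

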### Statistical Analyses

Patient characteristics will be summarized using descriptive statistics with frequency, mean, and standard deviation. The following items will be evaluated: sex, age, symptoms suggestive of pancreatic cancer (abdominal pain, jaundice, back pain, and weight loss), newly diagnosed or worsening of type 2 diabetes, family history of pancreatic cancer, abnormal laboratory test value for serum amylase (high or low) or serum CA19-9 (high), pancreatic duct dilation, or pancreatic cyst detected by echography. Participants’ BMI and smoking status will also be recorded for use in adjusted analyses.

Loss of participants to follow-up will be minimized by monitoring missed appointments and contacting participants promptly. Where key data items are unavailable or only partially reported, we will use multiple imputation to impute missing data where indicated.

Data on patients with a confirmed diagnosis will be summarized using descriptive statistics according to resectability classification [16]. Binomial logistic regression analysis (both univariate and multivariate analyses) will be performed with a diagnosis of pancreatic cancer as the objective variable and each risk factor and the result of an imaging test as explanatory variables. For the primary multivariable analysis, variables will be selected with a two-sided significance level of 5%. In addition to the unadjusted analyses, logistic regression analyses adjusted for BMI and smoking status will be conducted.

Sensitivity analysis will be conducted to generate multivariable prediction scores based on all available risk factors, regardless of performance or significance on univariable analysis, and based on alternate combinations of risk factors as indicated. Formal comparisons of the relative goodness-of-fit of each model will be conducted through derivation of the Akaike Information Criteria and/or the Bayesian Information Criteria as indicated. We will compare the performance of the prediction score based on this primary model against those of the sensitivity analysis models.

No interim analysis or subgroup analysis will be performed. A separate follow-up study will be conducted to evaluate the 5-year survival rate of pancreatic cancer in the region. SPSS statistical software (Version 25.0, IBM Corp) will be used for all analyses.

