## Methods

### Study Design and Population

This is a prospective, multicenter, observational cohort study for the early detection of pancreatic cancer in Japanese patients. The study was initiated in September 2020 and aims to recruit at least 150 patients. The aim of the study is to assess whether using a scoring metric to screen for known pancreatic cancer risk factors will improve the rate of early identification in this patient population. The flowchart of patient enrolment and evaluation is summarized in Figure 1. The study is registered in UMIN-CTR Clinical Trials Registry (UMIN000041624). Patients who seek consultation at one of five participating local clinics in the Tsu City area until September 30, 2022, will be referred through the regional medical reference system to the Faculty of Medicine, Gastroenterology, and Hepatology at Mie University Graduate School for a detailed examination for pancreatic cancer. 

Prespecified risk factors and associated point scores will be assessed as follows: symptoms (abdominal pain, jaundice, back pain, or weight loss): 1 point; newly diagnosed diabetes mellitus (type 2) or worsening of diabetes: 1 point; family history of pancreatic cancer (parent, child, or siblings, including other types of pancreatic neoplasms): 1 point; abnormal serum amylase level (under 44 U/mL or over 132 U/mL): 1 point; elevated serum CA19-9 level (>37 U/mL [15]): 1 point; pancreatic duct dilation (>3 mm) or pancreatic cyst detected by abdominal ultrasound: 2 points [11]. Adults aged 20 years or older scoring ≥2 points on this metric for prespecified pancreatic cancer risk factors will be eligible for inclusion (those scoring 2 or less but at high risk for pancreatic cancer will be referred for follow-up, but not included in the study). The total number of patients diagnosed with pancreatic cancer and the subsets of patients with surgically resectable pancreatic cancer and Stage 0/I pancreatic cancer will be determined (Figure 1). After registration, participants will undergo hospital visits every 6 months for a period of 2 years.

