## Discussion

The detection of pancreatic cancer, particularly at the early stages when 5-year survival rates are relatively high, remains challenging. Despite advancement in the knowledge of potential risk factors that cause pancreatic cancer and newly available tools for early diagnosis, its incidence is increasing and is estimated to include 355,317 new cases per year up to 2040 [17]. Previous studies have revealed the value of using clinical findings to detect early pancreatic cancer [12-14]. Sakamoto et al [14] found that of the five clinical findings they investigated, three (symptoms, new onset diabetes, and high CA19-9) were more frequent in the advanced pancreatic cancer group than in the early and non–pancreatic cancer groups. In contrast, high amylase and/or high pancreatic amylase levels were significantly more frequent in the early pancreatic cancer group than in the other groups. Similarly, CA19-9 levels >37 U/mL had a sensitivity, with 95% specificity, of 68% and 53% for detecting pancreatic cancer at >1 year and >2 years before diagnosis, respectively [18].

We plan to initiate a prospective, observational study designed to evaluate a scoring metric for systematic early detection of pancreatic cancer in Mie Prefecture, Japan. If demonstrated to be effective, our system may represent a novel tool for use in the diagnosis and subsequent management of this patient population. A strength of our study is that, although patients will be referred from five different participating centers, all diagnostic and follow-up assessments will be performed at a single institution, eliminating variability in local practices. A possible limitation is that, for ethical reasons, this study will not directly compare the scoring metric with no scoring in terms of new diagnoses. However, the rates of diagnoses, particularly of early stage pancreatic cancer, can be compared with historic published data. Additionally, with a relatively small sample size, this initial study will be limited in its ability to be applied to the wider population and different ethnicities because most of the participants are likely to be Japanese. A planned future study will examine 5-year survival after referral using the scoring metric and the value of each item in the scoring metric for detecting early stage pancreatic cancer in a larger number of patients.

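### Amylase appears to be modelled as one low-or-high item and CA19-9 as a single cut-off, so the regression cannot show whether low amylase earns its point and loses part of the CA19-9 signal (minor)

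*Protocol article*

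**What the plan says.** Study Design and Population defines the scored risk factors. Two are laboratory items: "abnormal serum amylase level (under 44 U/mL or over 132 U/mL): 1 point" and "elevated serum CA19-9 level (>37 U/mL [15]): 1 point". Low and high amylase therefore share a single point, and CA19-9 counts only as above the cut-off or not.

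Statistical Analyses carries the same wording into the list of items to be evaluated: "abnormal laboratory test value for serum amylase (high or low) or serum CA19-9 (high"). The logistic regression is run "with a diagnosis of pancreatic cancer as the objective variable" and takes "each risk factor and the result of an imaging test as explanatory variables". For the primary multivariable model, "variables will be selected with a two-sided significance level of 5" percent. Sensitivity models use all available risk factors or are "based on alternate combinations of risk factors as indicated", and the models are compared by AIC and/or BIC.

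The Discussion reports from the earlier regional study that "high amylase and/or high pancreatic amylase levels were significantly more frequent in the early pancreatic cancer group". It cites nothing on low amylase.

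**The concern.** The article does not spell out how the laboratory items are coded in the regression. Since they are defined as single scored items and each risk factor is entered, the natural reading is one yes/no term per item. The planned alternate combinations recombine items; nothing says they split one.

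Two opposite abnormalities would then share one odds ratio, although the evidence cited is for one direction only. If low amylase is the weaker predictor, the pooled estimate understates the high-amylase association. With selection at 5% and few cancers expected, that could decide whether amylase stays in the primary model and its prediction score. Whatever the true effects, a pooled term cannot say whether low amylase deserves a point, which matters in a study meant to evaluate the metric.

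For CA19-9, a yes/no term treats every value above 37 U/mL alike. Some information is lost, and the question is how much.

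**Working it through.** **Inputs from the article.** Expected diagnosis rate 10%, planned size 150 and expected enrolment 160 to 240 (Sample Size). CA19-9 above 37 U/mL with sensitivity 68% and 53% at 95% specificity, more than 1 and more than 2 years before diagnosis (Discussion). The article gives no amylase odds ratios (OR), no share of participants with low or high amylase, and no share above the CA19-9 cut-off.

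**1. The plan's own figure.** n = 1.96² × 0.10 × 0.90 / 0.05² = 138.3, which agrees with the stated 138. It concerns only the precision of the diagnosis rate and does not depend on how the regression is coded.

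**2. Events.** 10% of 150 is 15 cancers; 10% of 160 to 240 is 16 to 24.

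**3. Amylase (illustration on assumed values).** With shares p among non-cases, the pooled OR against normal amylase is (p_high × OR_high + p_low × OR_low) / (p_high + p_low). With both shares 10%, OR_high = 3 and OR_low = 1, it is (0.30 + 0.10) / 0.20 = 2.00.

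Approximate power is Φ(ln OR / SE − 1.96), with SE² = 1/[15 p₁(1−p₁)] + 1/[135 p₀(1−p₀)], where p₁ and p₀ are the item's shares in cases and non-cases. In the same example:

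- High versus not high: p₀ = 0.10, p₁ = 0.30/1.20 = 0.25, SE = 0.662, 1.099/0.662 = 1.66, power 38%.
- Pooled: p₀ = 0.20, p₁ = 0.40/1.20 = 0.333, SE = 0.589, 0.693/0.589 = 1.18, power 22%.

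With high amylase in 10% of non-cases throughout:

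| OR high | OR low | Low share in non-cases | Pooled OR | Power, pooled | Power, high vs not high |
|---|---|---|---|---|---|
| 3 | 1 | 5% | 2.33 | 28% | 38% |
| 3 | 1 | 10% | 2.00 | 22% | 38% |
| 3 | 1 | 20% | 1.67 | 15% | 38% |
| 3 | 2 | 10% | 2.50 | 36% | 31% |
| 2 | 2 | 5% | 2.00 | 19% | 14% |
| 2 | 2 | 10% | 2.00 | 22% | 12% |
| 2 | 2 | 20% | 2.00 | 24% | 9% |

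Pooling hurts when low amylase is uninformative and helps when both directions carry similar risk. Power is low in every row.

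**4. CA19-9.** Fit an equal-variance binormal marker: separation d = z(sensitivity) + z(0.95), continuous AUC = Φ(d/√2), yes/no AUC = (sensitivity + 0.95)/2. Information kept is the ratio of mutual information (yes/no over continuous) at a 10% diagnosis rate.

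- Sensitivity 68%: d = 0.468 + 1.645 = 2.113; AUC 0.932 continuous, 0.815 yes/no; information kept 0.1114/0.1539 = 72%.
- Sensitivity 53%: d = 0.075 + 1.645 = 1.720; AUC 0.888 continuous, 0.740 yes/no; information kept 0.0729/0.1122 = 65%.

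The loss is therefore 28% to 35%.

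**5. A different model for comparison.** For a normal marker with a small effect, the share kept is φ(z_q)²/[q(1−q)], where q is the proportion above the cut-off: 64% at q = 50%, 49% at 20%, 34% at 10%. The loss exceeds half only when roughly 20% or fewer are above the cut-off.

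**The case against.** The strongest reply is that the coding is inferred. The amylase wording with both directions stands in the list of items to be summarised and could mean that direction is tabulated. A condensed article may leave covariate coding to a full plan that is not shown. That stands as a caution: if the full plan already separates the directions, the amylase part falls away.

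Modelling the items as scored is also defensible, because the aim is to evaluate this metric. Recoding them in the primary model would evaluate a different tool, and with about 15 to 24 cancers an extra sparse term has a price. That stands too, and it is why the primary model should not change.

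Three stronger readings are tempting, but the documents do not support them:

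- A reader might infer that the cut-off discards most of the CA19-9 information, so that 15 cancers inform the term like 5 to 7 (15 × 0.34 = 5.1; 15 × 0.49 = 7.3). That needs a small effect and only 10% to 20% of participants above 37 U/mL. The article gives no such share, and its cited sensitivity and specificity imply a strong effect. CA19-9 also counts towards entry, so a larger share is plausible.
- A reader might infer that high amylase is the only marker tied to early disease. That holds only within the five-finding study; the Discussion also cites CA19-9 above 37 U/mL one to two years before diagnosis.
- A reader might infer that pooling hides an early-cancer signal. The regression outcome is any pancreatic cancer, so splitting amylase would not make this model address early disease, and the article gives no odds ratio for high amylase and any cancer.

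**Conclusion.** The point holds as a minor one, on the natural reading that each scored item is one yes/no term.

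For amylase, dilution of the high-value association is conditional: it occurs if low amylase is the weaker predictor and is absent if both directions carry equal risk. Its size cannot be taken from the article; the tabulated odds ratios and shares are assumptions. What does not depend on them is that a pooled term cannot tell the two directions apart.

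For CA19-9, the loss is material, at about one third. That figure rests on the equal-variance binormal model and on carrying pre-diagnosis accuracy from another study over to participants selected by score.

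The primary endpoint, the diagnosis rate with its 95% CI, does not use this coding.

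**What to change.** Leave the entry score and the primary multivariable model, with items as scored, unchanged. In Statistical Analyses, before the final analysis:

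1. State how the amylase and CA19-9 items are coded in the regression.
2. Report diagnosis counts and univariate odds ratios separately for low and for high amylase, each against values within the limits.
3. Add to the planned sensitivity models one in which log-transformed CA19-9, from the measurement used for the entry score, replaces the yes/no item. Compare it with the primary model by AIC/BIC on the same participants.
4. If the number of cancers allows, add a sensitivity model with separate low and high amylase indicators.

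The cost is a little more analysis. Log CA19-9 replaces a term and adds no parameter; splitting amylase adds one sparse term to a thin model, which is why item 4 is conditional. Numeric results must exist for the cut-offs to be applied, but the article does not say that the entry values, rather than yes/no flags, reach the study database. If they do not, they would have to be retrieved.

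### The model behind the primary prediction score includes an imaging result that, on its natural reading, is the diagnostic work-up and is not known at referral

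*Protocol article*

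**What the plan says.** Statistical Analyses in the protocol article specifies a logistic regression "with a diagnosis of pancreatic cancer as the objective variable", with "each risk factor and the result of an imaging test as explanatory variables". For the primary multivariable model, "variables will be selected with a two-sided significance level of 5" per cent. A prediction score is then based on that model and compared, using AIC and/or BIC, with sensitivity scores built from the full set of risk factors or from other combinations of them.

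Three other sections bear on what the imaging term is:

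- Study Design and Population already has an imaging item in the referral score: "pancreatic duct dilation (>3 mm) or pancreatic cyst detected by abdominal ultrasound: 2 points". Statistical Analyses lists it again among the baseline items.
- Diagnostic Procedures says that the data collected at the university hospital "will include the outcomes of routine EUS, dynamic CT, and MRI or magnetic resonance cholangiopancreatography assessments". It continues: "Confirmatory diagnostic tests will include endoscopic retrograde cholangiopancreatography and endoscopic ultrasound-guided fine needle aspiration", with "cell block analysis to obtain histological diagnosis using hematoxylin and eosin staining".
- Follow-Up Assessments says: "Patients with negative diagnostic results will be followed by contract CT, abdominal ultrasound, and/or MRI". Blood tests are added every 6 months. No pathology is mentioned for these patients.

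**The concern.** The stated aim is to learn whether a score made of items known at the clinic helps to find pancreatic cancer earlier. The regression should therefore relate the diagnosis to those items. If the imaging term is the hospital work-up, it differs from the other predictors in two ways.

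First, it is part of the route to the outcome. Imaging influences who goes on to ERCP or EUS-FNA, and a patient with negative results is classed as a non-case largely on further imaging. Predictor and outcome are then linked by the conduct of the study as well as by biology.

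Second, it does not exist when the referral decision is made. A score that contains it cannot be used by the referring clinic.

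Three results are at stake: the adjusted coefficients of the six referral items, the make-up of the primary prediction score after selection, and the comparison of that score with the sensitivity models. A model with work-up imaging can fit better than a model without it for reasons that say nothing about the referral items.

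**Working it through.** **1. Which imaging?** The score has six items: symptoms, diabetes, family history, amylase, CA19-9, and the clinic ultrasound finding. The ultrasound finding is thus covered by the words about each risk factor. An imaging result named in addition to these is most naturally EUS, dynamic CT or MRI/MRCP. The article gives no modality, time point or coding for it.

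**2. How many cancers?** The article's own calculation comes first. With an expected rate of 10% and a half-width of 5 points, n = 1.96² × 0.10 × 0.90 / 0.05² = 138.3. This reproduces the stated 138 (139 if rounded up). Expected cancers at 10% are 150 × 0.10 = 15 at the planned size, and 16 to 24 at the expected enrolment of 160 to 240. At the rate in the cited earlier study (28/224 = 12.5%), 150 to 240 participants would give about 19 to 30.

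**3. How likely is a zero cell?** If the imaging variable has sensitivity s for eventual diagnosis, the chance that none of e cancers is imaging-negative is s^e. The chance of at most one is s^e + e(1 − s)s^(e−1). The article gives no sensitivity, so s is an assumption and is varied. The last column comes from a simulation with N = 150, 10% cancers and 400 data sets per setting. It fits the six items plus a binary imaging term with specificity 0.70 to 0.95. Item prevalences were assumed between 0.10 and 0.60 and item odds ratios between 1.5 and 3, with items independent given the outcome.

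| Assumed s | No imaging-negative cancer, e = 15 | At most one, e = 15 | None, e = 24 | Simulated data sets with separation |
|---|---|---|---|---|
| 0.80 | 3.5% | 17% | 0.5% | 16–24% |
| 0.90 | 21% | 55% | 8% | 36–48% |
| 0.95 | 46% | 83% | 29% | 55–62% |
| 0.98 | 74% | 96% | 62% | 79–83% |
| 1.00 | 100% | 100% | 100% | 100% |

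The same six-item model without imaging was separated in about 12% of data sets. The imaging term therefore adds little at s = 0.80 and a great deal from about 0.95 upward.

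**4. How stable is the estimate when it is finite?** Take 15 cancers, 135 non-cancers and expected (fractional) cell counts.

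- s = 0.95, specificity 0.90: OR = (14.25 × 121.5)/(0.75 × 13.5) = 171. SE of log OR = √(1/14.25 + 1/0.75 + 1/13.5 + 1/121.5) = 1.22. The 95% CI is about 16 to 1865.
- s = 0.80, specificity 0.70: OR = (12 × 94.5)/(3 × 40.5) = 9.3, 95% CI 2.5 to 35.

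Both lower limits exceed 1. On these expected counts the imaging term would pass selection at 5% in a single-variable model even with modest accuracy, and could then take the place of weaker referral items in the multivariable model.

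**5. What does the score comparison then measure?** The sensitivity scores are described in terms of risk factors. If they leave out work-up imaging and the primary model keeps it, the AIC/BIC difference mainly measures the diagnostic value of EUS, CT or MRI, not the choice of referral items.

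**The case against.** The strongest reply is that the sentence is only ambiguous. The sole imaging item in the variable list of Statistical Analyses is the clinic ultrasound finding. The phrase could mean five non-imaging items plus that finding, entered once. On that reading there is no double entry and the circularity is far weaker. The reading is possible, so it cannot be said that the sentence is wrong however it is read. But Study Design and Population counts the ultrasound finding as a risk factor, which makes the work-up the more natural meaning, and nothing in the sentence keeps the work-up out.

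A reader might also infer that the diagnosis is simply made by imaging. The document does not support that: it names confirmatory tests with cytology and cell-block histology, and patients negative at first are seen again over 2 years. The bias arises from who is sent for confirmation and how negatives are settled.

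A reader might further infer that the model is bound to be separated. That holds only if every diagnosed patient is coded imaging-positive. It is not to be expected for a single modality, an indirect sign, or baseline imaging with cancers found later.

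Finally, the reach is limited. The primary endpoint is a diagnosis rate that this model does not touch, the univariate analyses of each item are unaffected, and the Discussion leaves the value of each item to a larger future study. All of this stands and limits the severity. It does not justify putting a work-up result into the model behind the primary prediction score. That is a stated choice of predictor, not a detail left to a fuller document.

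**Conclusion.** The concern holds in a limited form. On its most natural reading, the plan lets the EUS, CT or MRI/MRCP work-up enter the model from which the primary prediction score is taken. This brings verification and incorporation bias, can push out referral items under 5% selection with about 15 to 24 expected cancers, yields a score that cannot be computed at referral, and distorts the comparison with the sensitivity models.

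Separation or very wide intervals are a conditional further risk. In the simulation with about 15 cancers, separation becomes more likely than not at a sensitivity of about 0.95 or more, which is plausible only for something like a combined work-up result. The sensitivities, specificities, item prevalences and item odds ratios are all assumptions. The argument about use at referral depends on none of them: even a stable imaging coefficient would answer a different question. The change should be made before analysis, but the diagnosis rate, its confidence interval and the sample size are not affected.

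**What to change.** Replace the sentence on explanatory variables with one to this effect: the primary multivariable model and all referral prediction scores use only items known at referral, namely the six score items with the clinic ultrasound finding counted once; BMI and smoking status are added in the adjusted analysis.

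Report the work-up imaging separately, either as positives and confirmed cancers per modality or in a distinct model labelled as diagnostic, with modality, time point and coding defined. Imaging need not be removed from every analysis, because which findings accompany confirmed cancer is a legitimate secondary question.

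With so few cancers, even the six-item model can separate (about 12% of simulated data sets under the assumptions above). A penalised method such as Firth's would be a sensible optional addition.

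The cost is one sentence in Statistical Analyses, with no new data and no change to sample size or primary endpoint. The drawback is that the primary model's apparent fit will look less favourable.
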